#### Qualitative data - semi-structured VSR interviews with patients and practitioners

Patient VSR interview transcripts will be analysed using inductive thematic analysis, where codes and themes are generated from data based on individual reflections, perceptions and experiences (Table 4). This will be completed separately for QRISK®2 and JBS3 groups for comparison. The resulting thematic map for each group will provide insight into patient perceptions and understanding of CVD risk (Obj. 3), with video-stimulated reflections on that experience, and further reflections on their thoughts, feelings and intentions to undertake health-protective behaviour following the Health Check (Obj. 4). Data will also allow inferences about the underlying mechanisms (Obj. 5).

Similarly, inductive thematic analysis will be used to analyse practitioner VSR interview transcripts, separately for QRISK®2 and JBS3 groups. The resulting thematic map for each group will provide insight into their perceptions and understanding of CVD risk (Obj. 3), with video-stimulated reflections on aspects such as how they communicate risk in consultations, their use of the calculator, the types of advice they offer, patient responses (Obj. 4), allowing inferences about the underlying mechanisms (Obj. 5).

#### Quantitative - content of health check consultations

The content of the recorded consultations will be characterised using a coding framework that involves second-by-second coding of Health Check content. The framework comprises 36 items grouped in to six categories (patient-practitioner communication, general Health Check processes, risk dialogue, CVD risk factors, lifestyle interventions, medical interventions). The resulting data will provide aggregate indicators for each consultation to allow between-group comparisons (e.g., proportion of Health Check considered practitioner- or patient-dominated; proportion of time discussing risk; proportion of time discussing intervention/changes; number of times the practitioner manipulated the risk score to illustrate amenability of risk to change).

The development of the coding process and guide was iterative. Four “mock” Health Checks were undertaken by practitioners and PPI volunteers. These were video-recorded and two researchers (LC; NE) coded the consultations by consensus to reach consistency in approach. A third researcher (VR) then coded all four consultations independently. Intraclass Correlation Coefficients (ICCs) were calculated and demonstrated excellent inter-rater reliability (ICCs ranged from .968 to .995). The resulting framework will be refined during a training/checking phase with study data, whereby an additional four recorded Health Checks (2% of total) will again be independently coded by two researchers and inter-rater agreement assessed. Once finalised, two researchers (LC; VR) will code the remaining Health Check recordings independently (118 each). For every 20 coded consultations (8% of total), two would be subject to independent verification (independent coding and calculation of ICCs). This will mitigate the risk of coder drift throughout the study and provide independent verification of 10% of consultations overall.

A between subjects t-test or non-parametric equivalent will be used for between-group comparisons of key outcomes for Health Check content (e.g., proportion of time spent discussing CVD risk). To explore possible cohort effects within the data, ICCs will be calculated (i.e., to examine possible clustering within practices). Multi-level modelling is not appropriate; the study is designed to allow for novel qualitative enquiry and is not powered for multi-level statistical analysis.

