### Sample size

A priori determination of sample sizes for qualitative research is a point of contention [45, 46]. For the present study, it was necessary to estimate requirements for the patient VSR interviews and use this to inform the total number of recorded Health Checks required per practice. As summarised in Table 3, 48 VSR patient interviews (24 per group, 4 per practice) will allow patient sampling stratified by gender, age and CVD risk, and provide a sample size that compares favourably with studies using VSR or audio-recordings of primary care consultations (ranging from *n* = 9–44 [42, 43]). These 48 recorded Health Checks will be selected (with stratification) from 144 (72 per group, 12 per practice) that are subject to deductive qualitative analysis; i.e., 12 per practice was deemed sufficient to allow stratified sampling of four patients per practice. To obtain the 144 recorded Health Checks that are suitable for qualitative analysis, we will aim to record 240 (120 per group, 20 per practice). This oversampling will serve two purposes. First, it will allow for exclusions due to non-attendance, technical issues and Health Checks that contain little or no discussion of CVD risk. Second, with 120 consultations per group, using a between subjects t-test with a two-tailed probability and alpha of .05, we will have statistical power of at least .8 to detect a small to medium effect (Cohen’s d) = 0.37. It will also mean that the effect sizes derived from the study will have good levels of precision for estimating the effect sizes in future studies and so provide more accurate power analysis for such studies.

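### ICCs from two of every 20 consultations are a weak check for coder drift in the consultation-level indicators; the same double-coded recordings would support a better one

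*Protocol article*

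**What the plan says.** All of this is in the Protocol article, Data analysis, under Quantitative - content of health check consultations, unless another section is named.

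- **Mock checks.** Two researchers coded four mock Health Checks by consensus and a third "coded all four consultations independently". The article says the ICCs "demonstrated excellent inter-rater reliability (ICCs ranged from .968 to .995". It gives no interval, ICC form or unit of rating.
- **Checking phase on study data.** Next, "an additional four recorded Health Checks (2% of total) will again be independently coded by two researchers", with agreement assessed and the framework refined.
- **Main coding.** Two researchers "will code the remaining Health Check recordings independently (118 each").
- **Ongoing verification.** "For every 20 coded consultations (8% of total), two would be subject to independent verification (independent coding and calculation of ICCs"). Its stated purpose: "This will mitigate the risk of coder drift throughout the study and provide independent verification of 10% of consultations overall".
- **Coding structure.** "The framework comprises 36 items grouped in to six categories", coded second by second and then reduced to aggregate indicators per consultation, which are compared between groups by t-test or a non-parametric equivalent.
- **Total.** Under Sample size: "we will aim to record 240 (120 per group, 20 per practice").

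**The concern.** An ICC sets variation between the rated units against disagreement between coders, so its meaning depends on the unit. The between-group tests use one value per consultation, and reliability therefore needs to be shown at that level. Two consultations give one degree of freedom between units. The alternative is to take the ICC within a consultation, across items. That supplies many units, but most of the variation is then between items that take long and items that hardly occur, and this can swamp a change in how one item is coded.

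Apart from the double-coded recordings, every content outcome rests on one coder's reading. If the coding of risk talk shifted over the study, the planned check might not reveal it, and the shift would enter the comparisons for which the Sample size section claims power.

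**Working it through.** **Inputs from the article.** 240 recordings; 4 mock checks; 4 study recordings double-coded in the checking phase; 2 of every 20 verified afterwards; 36 items; pilot ICCs .968 to .995.

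**The plan's own counts reproduce.** 4/240 = 1.7% (stated as 2%); (240 - 4)/2 = 118 each; 20/240 = 8.3% (stated as 8%); 2/20 = 10%. That makes 240/20 = 12 batches and about 24 verified recordings (236 x 0.10 = 23.6). The pilot ICCs cannot be reproduced, as no data are given.

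**Reading 1: the unit is the consultation.** Assume two ratings per unit and a single-measure ICC r.

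- F = (1 + r)/(1 - r). For r = .968, F = 1.968/0.032 = 61.5. For r = .995, F = 1.995/0.005 = 399.
- Lower limit = (L - 1)/(L + 1), where L = F / F(.975; n-1, d) and d = n (one-way) or n-1 (two-way). The upper limit uses F x F(.975; d, n-1) in the same way.
- n = 2, two-way: L = 61.5/647.8 = 0.095, limit = -0.905/1.095 = -0.83.
- n = 2, one-way: L = 61.5/38.51 = 1.597, limit = 0.597/2.597 = 0.23.
- n = 4, two-way: L = 61.5/15.44 = 3.983, limit = 2.983/4.983 = 0.60.
- n = 4, one-way: L = 61.5/9.979 = 6.163, limit = 5.163/7.163 = 0.72.

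| Observed ICC | Consultations | Two-way 95% CI | One-way 95% CI |
|---|---|---|---|
| .968 | 2 (one batch) | -0.83 to 1.00 | 0.23 to 1.00 |
| .968 | 4 (mock checks) | 0.60 to 0.998 | 0.72 to 0.998 |
| .995 | 4 (mock checks) | 0.93 to 1.00 | 0.95 to 1.00 |
| .968 | 24 (pooled) | 0.93 to 0.99 | 0.93 to 0.99 |

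Power to detect a fall from .968 (one-sided 5% F test, one-way ICC):

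| Consultations | Fall to .90 | Fall to .80 | Fall to .50 |
|---|---|---|---|
| 2 | 9% | 13% | 22% |
| 12 | 60% | 93% | >99% |
| 24 | 87% | >99% | >99% |

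With a true ICC of .80, a batch of two still shows .90 or more about 28% of the time.

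**Reading 2: the unit is the item within a consultation.** Treating the 36 items as independent (an assumption), an observed .968 has a 95% CI of 0.94 to 0.98 for one recording and 0.95 to 0.98 for two (72 units). Power against a general fall to .90 is 96% and 99.9%. A general loss of agreement is therefore visible.

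Drift in a single item is another matter. A simulation with assumed spreads (36 lognormal items, median 30 seconds, log SD 1.2 between items and 0.3 between consultations) gives:

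- *General disagreement.* As coder log SD rises through 0.2, 0.3 and 0.5, the across-item ICC falls through about 0.94, 0.88 and 0.72.
- *Drift in one item.* With coder log SD 0.1, one coder halving a 60-second item moves the mean ICC only from about 0.985 to 0.982. In nearly nine runs in ten it stays above .968, the lowest value reported for the mock checks.

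The sizes depend on the assumed spreads. The mechanism does not: large differences between items outweigh a change in one of them.

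**The case against.** The strongest reply has four parts.

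1. **Unit and pooling are not stated.** The article does not say that ICCs are judged batch by batch, and a fuller protocol or coding guide may settle this. The point stands as far as it goes, so the silence is not itself the finding. The finding is that neither reading of a two-recording ICC does what the check is said to do for a single analysed indicator.
2. **There are more safeguards than the mock checks.** Four study recordings are double-coded before main coding, and verification accumulates to about 24. This also stands. Pooled, they are adequate for overall reliability, but a pooled ICC does not locate drift in time.
3. **The text promises to mitigate drift, not to test for it.** Fair: periodic independent recoding has value as quality control. The question is what the ICC adds to it.
4. **High across-item ICCs need not hide poor item reliability.** In the simulation model, across-item values of about .966 to .996 go with per-item reliability of about .79 to .97, or about .93 to .99 if the between-consultation log SD is 0.6 rather than 0.3. This limits the second reading to drift confined to one item.

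A reader might infer that neither sample can support the reliability statement or detect any drift. The documents do not support that. An across-item ICC does fall as general disagreement grows. At .995, even four consultations give a lower limit of 0.93 to 0.95. A reader might also infer that drift would bias the comparison of groups. Whole practices belong to one group, so a link is possible, but the article states neither the coding order nor how recordings are divided between coders, and no link is shown.

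**Conclusion.** The concern holds in a limited form. An ICC from a batch of two recordings does not reveal drift in a single consultation-level indicator: across consultations it is uninformative, and across items it can mask a change confined to one indicator. For the mock checks, if the unit is the consultation, the lower stated value (.968) has a lower limit of only 0.60 to 0.72, so 'excellent' is not secured across the whole stated range.

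The intervals assume two ratings per unit and a single-measure ICC. The masking figures rest on assumed spreads. The consequence is modest, because the content coding belongs to a process evaluation within a mainly qualitative study. The change is still worth making, since the recordings it needs are already to be double-coded.

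**What to change.** Keep the double-coding load as planned and change what is computed from it.

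- Name the few key indicators (for example time on CVD risk and time on intervention). For each, report the between-coder mean difference, limits of agreement and an across-consultation ICC with its 95% CI, on the accumulated verified recordings (about 24).
- As the drift check, plot the signed coder difference for each key indicator against coding order.
- State the unit and form of every ICC reported.
- Give the interval beside 'excellent' for the four mock checks.

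The cost is a few lines of analysis and a less favourable reliability statement. No further coding is needed.

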**Methods:**

RIsk COmmunication in NHS Health Check (RICO) is a qualitative study with quantitative process evaluation. Twelve general practices in the West Midlands of England will be randomised to one of two groups: usual practice, in which practitioners use QRISK®2 to assess and communicate CVD risk; intervention, in which practitioners use JBS3. Twenty Health Checks per practice will be video-recorded (*n* = 240, 120 per group), with patients stratified by age, gender and ethnicity. Post-Health Check, video-stimulated recall (VSR) interviews will be conducted with 48 patients (n = 24 per group) and all practitioners (*n* = 12–18), using video excerpts to enhance participant recall/reflection. Patient medical record reviews will detect health-protective actions in the first 12-weeks following a Health Check (e.g., lifestyle referrals, statin prescription). Risk communication, patient response and intentions for health-protective behaviours in each group will be explored through thematic analysis of video-recorded Health Checks (using Protection Motivation Theory as a framework) and VSR interviews. Process evaluation will include between-group comparisons of quantitatively coded Health Check content and post-Health Check patient outcomes. Finally, 10 patients with the most positive intentions or behaviours will be selected for case study analysis (using all data sources).

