## Methods/design

### Design and setting

This qualitative study, which includes a quantitative process evaluation, will be undertaken in 12 general practices in the West Midlands that already deliver NHS Health Checks. Six practice pairs, approximately matched on practice size and deprivation, will be randomly assigned to one of two groups: QRISK®2 (usual practice) - practitioners continue to use QRISK®2 to communicate CVD risk during Health Checks; JBS3 (intervention) - practitioners use the JBS3 CVD risk calculator following brief training about the platform, but no training will be provided about risk communication. Participating practices will video-record their NHS Health Checks using the allocated CVD risk calculator over until 20 useable consultations are recorded. As summarised in Fig. 2 and detailed below, data collection will comprise: (1) Video-recording NHS Health Check consultations; (2) Post-consultation video-stimulated recall (VSR) interviews with patients and practitioners within 2 weeks, using excerpts from recorded health checks to facilitate recall and reflection; (3) Patient medical record reviews 12-weeks post-Health Check to determine subsequent action (e.g., GP appointment, lifestyle referral, statin prescription).

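### Practices are randomised, but consultations are tested as if independent, so the planned t-tests overstate the evidence for a difference between QRISK2 and JBS3

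*Protocol article*

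**What the plan says.** **Allocation.** Under Design and setting, "Six practice pairs, approximately matched on practice size and deprivation, will be randomly assigned to one of two groups". The practice is the unit of randomisation, with six practices per group. Under Practitioners, Health Checks in a practice are usually delivered by one or two nurses or health care assistants.

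**Analysis.** Under Quantitative - content of health check consultations, "The resulting data will provide aggregate indicators for each consultation to allow between-group comparisons", and "A between subjects t-test or non-parametric equivalent will be used for between-group comparisons of key outcomes for Health Check content". The unit of analysis is therefore the consultation.

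**Clustering.** The same section plans ICCs to look for clustering within practices. It gives no rule by which an ICC would alter the test, the standard error or the interval. It then closes off adjustment: "Multi-level modelling is not appropriate; the study is designed to allow for novel qualitative enquiry and is not powered for multi-level statistical analysis".

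**Record review.** The section on the patient medical record review takes over the same approach for its between-group comparisons.

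**Sample size.** The Sample size section takes 120 consultations per group and, "using a between subjects t-test with a two-tailed probability and alpha of .05", says "we will have statistical power of at least .8 to detect a small to medium effect" of d = 0.37. That calculation treats the 120 as independent.

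**The concern.** Consultations in one practice share a practitioner, a clinic and a patient population. The outcomes named are the balance of talk between practitioner and patient, the share of time spent on risk, and how often the practitioner manipulates the score. These largely describe how a practitioner works, so consultations within a practice can be expected to resemble one another. A test on 240 supposedly independent consultations then mistakes differences between practices for differences between calculators.

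The reason given for not adjusting does not justify this. Low power is a statement about precision, and with twelve clusters it is the true state of the design. The consultation-level test appears to escape it only by using a standard error that is too small. Nor is a multi-level model the only remedy, because simple tests on practice summaries suit a small number of clusters.

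The study intends to recommend which tool to endorse, and it offers its effect sizes for planning later studies. Spurious differences and intervals that are too narrow would feed into both.

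**Working it through.** **Inputs from the article:** 12 practices, 6 per group; m = 20 consultations per practice; 120 per group; two-sided alpha 0.05; d = 0.37 with SD 1. **Assumed:** the practice ICC, which the article does not give; the range 0 to 0.30 is shown.

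**1. The plan's own figure.** With n = 120 per group the noncentrality is 0.37 × √(120/2) = 2.87 on 238 df. Power is 0.814 by the exact t distribution and 0.818 by the normal approximation. The stated 0.8 is reproduced, but only for ICC = 0.

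**2. Effect of clustering on the planned test.**
- Design effect: DE = 1 + (m − 1) × ICC = 1 + 19 × ICC.
- Effective sample size per group: 120/DE.
- True two-sided error rate of the unadjusted test: about 2 × [1 − Φ(1.96/√DE)].

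At ICC 0.05, DE = 1 + 19 × 0.05 = 1.95, effective n = 120/1.95 = 61.5, and 1.96/√1.95 = 1.40, which gives an error rate of 0.16. The planned standard error is 1/√1.95 = 0.72 of its correct size. At ICC 0.10 it is 1/√2.90 = 0.59.

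**3. A valid alternative.** For a t-test on practice means (6 against 6, 10 df), the standard error of the difference is √(2 × DE/120). At ICC 0.05 this is √(3.9/120) = 0.180, the noncentrality is 0.37/0.180 = 2.05, and power is 0.46.

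**4. Simulation.** 10,000 trials per ICC, normal outcomes, equal variances and no true difference:

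| ICC (assumed) | DE | Effective n per group | Planned t-test error: formula | Planned t-test error: simulated | Practice-mean t-test error: simulated | Practice-mean power at d = 0.37 | d detectable with 80% power |
|---|---|---|---|---|---|---|---|
| 0 | 1.00 | 120 | 5.0% | 5.2% | 5.2% | 0.73 | 0.40 |
| 0.01 | 1.19 | 101 | 7.2% | 7.7% | 5.4% | 0.66 | 0.44 |
| 0.02 | 1.38 | 87 | 9.5% | 9.9% | 5.3% | 0.60 | 0.47 |
| 0.05 | 1.95 | 62 | 16.0% | 16.0% | 5.0% | 0.46 | 0.56 |
| 0.10 | 2.90 | 41 | 25.0% | 24.5% | 4.8% | 0.33 | 0.68 |
| 0.20 | 4.80 | 25 | 37.1% | 37.4% | 4.6% | 0.22 | 0.88 |
| 0.30 | 6.70 | 18 | 44.9% | 45.4% | 4.6% | 0.17 | 1.04 |

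The non-parametric option has the same fault: a Mann-Whitney test on consultations rejects about 15% of the time at ICC 0.05 and 25% at 0.10. A paired test on the six within-pair differences stays near 5%.

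The power figures ignore the pair matching, which might recover some precision.

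**The case against.** **The study is mainly qualitative.** The objectives are exploratory, objectives 1 to 5 are tied to the thematic and case-study analyses, and the record review is described as exploratory and mainly there for context. No confirmatory primary outcome rests on the t-tests. This stands, and it limits the damage. It does not make the tests valid: the article chose formal testing, with an alpha, a power and a claim of good precision.

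**The ICC is unknown.** At 0.01 to 0.02 the error rate is only about 7% to 10%, and the highest rates need an ICC of 0.20 or more. This also stands, so the size must be stated conditionally. Even so, one or two practitioners per practice and outcomes that record their behaviour make a negligible ICC hard to assume.

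**Clustering will be examined.** The ICCs are planned, and avoiding multi-level models with twelve clusters is defensible. But nothing follows from the ICCs, and no cluster-level alternative is offered. The article does not propose testing for clustering first, and doing so would be a weak safeguard. At a true ICC of 0.05, a 5% test for clustering misses it about 48% of the time, although the miss rate falls to about 15% to 17% at 0.10 and about 2% at 0.20.

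**The practice-mean test has limits.** The 5% error rate was simulated with equal variances. Only the JBS3 practices are told to manipulate risk scores, so for that outcome the variances may differ sharply. With one variance near zero, the pooled 10-df test rejects about 7% of the time and the Welch version about 5%. This is a reason to use Welch, not to keep the consultation-level test.

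**Conclusion.** The concern holds. The article states the unit of randomisation, the test, the power for that test and an argument against adjusting it. This is therefore a stated method that does not fit the design, not a detail left to an analysis plan. The test is too liberal at any positive practice ICC. How liberal depends on an ICC that the document does not give: about 7% at 0.01, 16% at 0.05, 25% at 0.10 and 37% at 0.20, assuming normal outcomes and 20 consultations in every practice. The power claim fails with it, since power of 0.8 at d = 0.37 requires independent consultations. The quantitative comparison is only one input to the recommendation, but it should not be run as planned.

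**What to change.** 1. **Main test.** Replace the consultation-level test. For each outcome take the mean, or the proportion, in each practice (12 values), compare groups with a two-sample t-test (10 df), and report the difference with its 95% CI. Use the Welch version where variances may differ, as for the count of risk-score manipulations.
2. **Supporting test.** Analyse the six within-pair differences with a paired t-test (5 df), which follows the matched randomisation.
3. **ICCs.** Report the within-group ICC of each outcome with its confidence interval as a result, not as a check that decides whether clustering matters.
4. **Rationale.** Delete the sentence that offers lack of power as the reason for not adjusting. If multi-level models are still to be avoided, the reason to give is the small number of practices, with the practice-level analysis in their place.
5. **Sample size section.** Restate power and precision for twelve practices over a stated ICC range, for example 80% power for d = 0.56 at ICC 0.05 and d = 0.68 at 0.10, and withdraw the unqualified claim of good precision.
6. **Record review.** Apply the same rule to the medical-record comparisons.

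If the investigators prefer not to test, descriptive comparisons by practice without p-values would also be sound.

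**Cost:** changes to the analysis and sample-size wording only, with no new data and no change to recruitment. Intervals will be wider, fewer differences will be significant, and the stated power will fall.

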### Sample

#### General practices

General practices that meet the following criteria will be recruited: a) deliver NHS Health Checks; b) already use the QRISK®2 percentage risk score in Health Checks; currently (or willing to) deliver Health Checks in specific clinics to facilitate data collection; c) are signed up to the ‘incentive scheme’ implemented by the Clinical Research Network (CRN) to ensure the GP practice is ‘research ready’; d) are willing to participate.

General practices will be stratified using data on practice list size and deprivation level of the practice location [40] to provide a proxy measure of typical socio-economic status of the practice population (Table 1).

**Table 1 Tab1:** Stratified sampling of six practices per group based on deprivation and list size

	Deprivation	
Practice list size	Most deprived 50%	Least deprived 50%
Small-Medium (< 8000)	2 QRISK®2; 2 JBS3	2 QRISK®2; 2 JBS3
Large (≥8000)	1 QRISK®2; 1 JBS3	1 QRISK®2; 1 JBS3

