### Recruitment

#### Practice sampling

The CRN will facilitate practice sampling. Briefly, this will involve an initial email to ‘research ready’ practices inviting expressions of interest. To identify willing and eligible practices, those expressing interest will be followed up with telephone calls and visits as appropriate. Practice participation will be incentivised through financial reimbursement of service support costs and remuneration for completing all parts of the study. Following practice-level consent, practice pairs matched on size and deprivation (Table 1), will be randomly assigned to the QRISK®2 or JBS3 group using a random number generator in MS Excel. After randomisation, the research team will undertake an initiation meeting at the practices to provide further information and basic training for staff involved.

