#### Patient and practitioner sampling

There will be three levels of patient sampling.

1) Total sample (*n* = 240): To achieve the 144 recorded consultations suitable for qualitative analysis (12 per practice allowing for non-attendances and consultations with no/minimal discussion of CVD risk), Health Check clinics would be recorded until 20 recordings per practice (240 total) have been achieved. In each practice, searches of the patient database will identify the cohort of eligible patients who will be stratified according to gender, age and ethnicity to ensure representation from different demographic groups (Table 2).

**Table 2 Tab2:** Stratified sampling of the 20 patients per practice to be invited for recorded Health Checks

		Gender	
		Female	Male
Age (yr)	40–54 yr	4 (3 WBRI/1 BAME)	4 (3 WBRI/1 BAME)
	55–64 yr	3 (2 WBRI/1 BAME)	3 (2 WBRI/1 BAME)
	65–74 yr	3 (2 WBRI/1 BAME)	3 (2 WBRI/1 BAME)

WBRI, White British; BAME, Black, Asian, Minority Ethnic

2) Qualitative analysis (*n* = 144): Video recordings will be screened within 48 h of filming. This will involve quantitative coding of the content of the consultation to identify those suitable for qualitative analysis (12 per practice) and VSR interview (4 per practice). Where risk is not discussed by patient or practitioner, the patient’s data would not be used for either.

3) VSR interviews (*n* = 48): VSR interviews will be conducted with 48 patients (24 per group) sampled from the 144 recorded Health Checks, stratified by gender, age and CVD risk (Table 3).

**Table 3 Tab3:** Example of stratified sampling of VSR patient interviews per group based on age, CVD risk and gender

		CVD Risk^a^	
		Low (<10%)	Medium-High (≥10%)
Age (yr)	40–54 yr	2 m / 2 f	2 m / 2 f
	55–64 yr	2 m / 2 f	2 m / 2 f
	65–74 yr	2 m / 2 f	2 m / 2 f

^a^QRISK percentage 10-year risk would be used for stratification purposes for consistency across both groups

The proposed total of 144 recorded consultations (12 per practice) with 48 patient VSR interviews and 18 practitioner VSR interviews, is comparable with other studies using audio-recording of similar consultations to explore CVD risk communication in patients with psoriasis (*n* = 130 in 10 practices [42]) and the number of interviews in VSR studies (*n* = 9–39 [43]).

All practitioners who will deliver the video-recorded Health Check clinics will be asked to participate in VSR interviews.

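### Practices are randomised in pairs matched on list size and deprivation, but the planned two-sample test of individual consultations uses neither these factors nor the practice

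*Protocol article*

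**What the plan says.** **Design.** The Design and setting section states: "Six practice pairs, approximately matched on practice size and deprivation, will be randomly assigned to one of two groups". Practice sampling repeats it: "practice pairs matched on size and deprivation (Table 1), will be randomly assigned to the QRISK®2 or JBS3 group". Table 1, captioned "Stratified sampling of six practices per group based on deprivation and list size", crosses two list-size bands (below 8000; 8000 or more) with two deprivation halves and puts equal numbers from each group in every cell. Read together, randomisation is within matched pairs.

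**Analysis.** The section on the content of Health Check consultations states: "A between subjects t-test or non-parametric equivalent will be used for between-group comparisons of key outcomes". ICCs are to be calculated to look for clustering by practice, but they do not enter the test. Multi-level modelling is ruled out because the study is mainly qualitative and not powered for it. The medical record review section applies the same comparison to its outcomes. The Sample size section rests on the same test: "with 120 consultations per group, using a between subjects t-test with a two-tailed probability and alpha of .05", with power of at least 0.80 for d = 0.37.

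**Patient-level risk.** The Table 3 footnote reads: "QRISK percentage 10-year risk would be used for stratification purposes for consistency across both groups". That concerns sampling for the video-stimulated recall interviews. No section uses the score in a between-group comparison.

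**The concern.** An analysis should reflect the restriction placed on the randomisation. List size and deprivation were chosen for matching, presumably because they were expected to relate to how Health Checks run. Balancing them removes their contribution from the true sampling error of the group difference. An analysis that ignores them leaves that contribution in the estimated error, so the standard error is too large for the design used. The planned test also counts 240 consultations as independent although 12 practices are randomised, and that pushes the error the other way.

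At stake are the precision and the error rates of the process-evaluation comparisons. The Sample size section offers the resulting effect sizes as well-estimated inputs for future studies, and the Discussion expects the findings to inform which calculator is endorsed.

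**Working it through.** **Inputs from the protocol article:** 12 practices, 6 per group, 20 consultations each; 120 per group; two-sided alpha 0.05; d = 0.37 (SD = 1); cell counts from Table 1. **Assumed, because not given:** ICC 0.05 or 0.10; share of between-practice variance explained by the two Table 1 factors, none or half.

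**1. The plan's own figure.** Noncentrality = 0.37 × √(120/2) = 2.87 on 238 df, giving power 0.814 (normal approximation 0.818). The stated 0.80 therefore reproduces, but only for 240 independent consultations with no design factor.

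**2. Effect of Table 1 on the estimate.** Each group has 4 small-medium and 2 large practices, and 3 in each deprivation half. Both factors are exactly balanced against group. With all 12 practices contributing, the adjusted and unadjusted differences in practice means are the same number. Only the estimated standard error and the df differ.

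**3. Variance of a practice mean** = ICC + (1 − ICC)/20.
- ICC 0.05: 0.05 + 0.0475 = 0.0975
- ICC 0.10: 0.10 + 0.045 = 0.145

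The variance of the group difference is this figure × (1/6 + 1/6), that is, divided by 3.

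**4. Factors explain half of the between-practice variance.** The true residual variance is 0.025 + 0.0475 = 0.0725 (ICC 0.05) or 0.05 + 0.045 = 0.095 (ICC 0.10). The SE is √(0.0725/3) = 0.155 or √(0.095/3) = 0.178. An unadjusted practice-level test leaves the factor variance in its error. Its expected residual variance is 0.0725 + 12 × 0.025/10 = 0.1025, or 0.095 + 12 × 0.05/10 = 0.155. The SE it reports is then about 0.185 or 0.227, which is too large.

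**5. Simulated results, 6 v 6 practice means.**

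| ICC | Share explained | Power, unadjusted (10 df) | Power, two covariates (8 df) | Type I error, unadjusted | Type I error, adjusted |
|---|---|---|---|---|---|
| 0.05 | half | 0.43 | 0.55 | about 0.02 | 0.05 |
| 0.10 | half | about 0.28 | 0.45 | about 0.02 | 0.05 |
| 0.05 | none | 0.46 | 0.44 | 0.05 | 0.05 |
| 0.10 | none | 0.33 | 0.32 | 0.05 | 0.05 |

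The price of the two covariates is the critical t, which rises from 2.23 to 2.31, a confidence interval about 3.5% wider.

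**6. The planned consultation-level test.** When 0, 30 or 60% of the between-practice variance is shared within pairs, its simulated type I error is 0.17, 0.13 or 0.09 at ICC 0.05, and 0.25, 0.20 or 0.13 at ICC 0.10. Adding the Table 1 factors to a consultation-level test would not cure this; the unit must change as well.

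**7. Patient-level adjustment.** Suppose patient covariates explain 20 to 40% of the within-practice variance only.
- ICC 0.05: variance falls from 0.0975 to 0.0880 or 0.0785; SE falls 5 to 10%.
- ICC 0.10: variance falls from 0.145 to 0.136 or 0.127; SE falls 3 to 6%.

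**The case against.** The strongest reply is that leaving out matching factors does not bias a randomised comparison. The study is mainly qualitative, names no primary quantitative outcome, and describes the record review as exploratory. Covariate lists usually belong in an analysis plan. This stands as to importance: the loss is in precision and error rates. It does not dispose of the point, because the article names the test, bases its power on it and argues against one alternative. That is a stated method, not an omitted detail.

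Several stronger readings are tempting, and the document does not support them.

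- *The matching calls for a strictly paired test.* With six pairs this leaves 5 df. At ICC 0.10 with useless matching, simulated power is 0.28 paired against 0.33 unpaired. Two covariates at 8 df are the safer use of the design.
- *Patient covariates would cut the standard error by 11 to 23%.* This follows from √(1 − 0.2) = 0.894 and √(1 − 0.4) = 0.775, but it needs the covariates to explain between-practice variance to the same degree. Nothing supports that.
- *Age, gender and ethnicity should also be adjusted for.* Table 2 sets the same quotas in every practice, so if they are met the adjustment changes the practice comparison little.
- *Chance imbalance in CVD risk is likely.* It is possible, but not shown. The Background says that QRISK2 depends heavily on age and gender, which Table 2 fixes. Patients already known to be at 20% risk or more are excluded, and deprivation is matched.
- *QRISK2 is held for all 240 patients.* The Table 3 footnote implies that it is available in both groups but does not say so for every recorded patient.

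**Conclusion.** The point holds in a limited form. The randomisation is restricted by list size and deprivation, and the fixed test ignores both these factors and the practice. Against an unadjusted practice-level test, using the two Table 1 factors gains about 12 power points at ICC 0.05 and about 17 at ICC 0.10 if they explain half of the between-practice variance. It also brings the type I error from about 0.02 back to 0.05. If they explain nothing, it costs 1 to 2 points. The ICC and the explained share are assumptions.

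A reader might infer that the missing factors account for the gap between the stated 0.80 and the power really available. They do not: even with useful covariates, power is 0.45 to 0.55 in these scenarios. Most of the gap comes from clustering, which is a separate and larger matter. Nor is the estimated difference biased by the omission. What is affected is precision and error rates in an exploratory process evaluation.

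**What to change.** In the section on the content of Health Check consultations, and by reference in the medical record review section:

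1. Replace the consultation-level test with a comparison of the 12 practice means (or other practice-level summaries, such as proportions) by linear regression on group, list-size band and deprivation half, with 8 df.
2. Keep the unadjusted practice-level difference (10 df) as a sensitivity analysis.
3. State whether QRISK2 10-year risk will be recorded for every recorded patient in both groups. If so, prespecify it as a patient-level covariate: regress the consultation outcome on it without a group term, then carry the practice mean residuals into step 1.
4. Restate the power claim for the analysis adopted, over a stated range of ICCs.

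The cost is a change of wording and 2 df. List size and deprivation are known at randomisation, so steps 1 and 2 need no new data; step 3 depends on the QRISK2 score being available. The objection to multi-level modelling is respected, since none is used.
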